## Abstract

**Background:**

There are no clear criteria for decision-making after proximal humeral fractures, and the choice of surgical strategy and, in particular, timing is controversial. Vascular disruption can lead to delayed avascular necrosis of the humeral head, which may result in failure of the fixation procedure and the need for revision surgery. MRI pulse sequences with zero echo time (ZTE) provide “CT-like” images of the bone, while dynamic contrast-enhanced MRI (DCE MRI) allows for visualization and quantification of vascular permeability, blood flow, and clearance rates within the bone. We hypothesize that MRI with a ZTE sequence is non-inferior to CT in terms of fracture morphology specification and that DCE MRI is suitable for quantifying perfusion of the humeral head after a proximal humeral fracture.

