**Discussion:**

As the optimal treatment method and timing of proximal humeral fractures are still controversial, the results of this study might help surgeons decide on the optimal treatment. The first aim is to evaluate the ZTE MRI sequence for its ability to assess fracture morphology compared to CT imaging. In this way, it can be decided whether or not the ZTE sequences can be considered as an alternative to CT imaging in proximal humeral fractures. The second aim of the study is to investigate the feasibility of DCE MRI for quantifying perfusion of the humeral head over a six-month period after proximal humeral fracture and ORIF with a locking plate. If the initial DCE MRI shows restricted perfusion of the humeral head, the risk of avascular necrosis may be increased, so it may be beneficial for the patient to proceed directly to reverse shoulder arthroplasty (RSA) instead of osteosynthesis with the risk of later revision. The data obtained from this study are required for the planning of a randomized trial.

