While MRI is routinely chosen for the visualization of soft tissue rather than bony structures, recent developments broaden the field of application for this technique. Firstly, the possibility to apply MRI pulse sequences with ultrashort echo-time (UTE) or even zero echo-time (ZTE) enables imaging of tissues with very short T2/T2* relaxation times and low proton density like the cortical bone [17]. After post-processing, these sequences yield “CT-like” images of bones and have shown their potential value in assessing bone structures when compared to CT imaging in various locations in both, the upper and lower extremity [18–20].

Secondly, dynamic contrast-enhanced MRI (DCE MRI) enables the visualization and quantification of vessel permeability, blood flow, and clearance rates even within bone [21–26].

We hypothesize that *(i)* an MRI including a ZTE sequence is not inferior compared to CT with regard to the detection of fracture lines and specification of fracture morphology and that *(ii)* DCE MRI is suitable for quantifying humeral head perfusion after a proximal humeral fracture.

Because either one of these hypotheses is worth to be investigated within clinical studies, there is the scientific need to conduct an exploratory study first. This will not only provide the data necessary to sharpen the design of a subsequent clinical investigation but will also help to integrate the study investigations into the clinical routine.

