## Methods / Design

### Aim of the study

This study aims *(i)* to evaluate a ZTE bone sequence (oZTEo, Signa Premier, General Electric Healthcare, Waukesha, Wisconsin, USA) for the assessment of fracture geometry and concomitant injuries compared to CT as the standard of care, *(ii)* to gain insights into the benefit of a pre-operative DCE MRI for prediction of humeral head perfusion, and *(iii)* to evaluate the humeral head perfusion at 3 and 6 months postoperatively. To this end, the correlation between perfusion data based on DCE MRI, the clinical (scores), and radiological findings (conventional radiographs, CT) as well as the intraoperative findings (biopsy) will be investigated. In parallel, we will compare the preoperative CT and ZTE MRI-based findings with regard to the value for fracture classification. This comparison is indispensable to assess the power of ZTE MRI as a substitute for CT imaging and thus to reduce radiation exposure. Regarding DCE MRI, patients with proximal humeral fractures may benefit from improved preoperative diagnostics and information on the perfusion of the humeral head. This could allow for an individualized decision on optimal treatment and as such may help to reduce the risk for revision surgery.

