### Sample size justification

Due to the fact that this is an explorative study on the feasibility of the imaging techniques mentioned above, sample size calculation was omitted [28]. However, a minimum sample size of 20 participants is recommended, as published elsewhere [29]. As we do not know if the results obtained via DCE MRI fit those obtained via histological examination of the biopsy we are considering investigating a total of 30 patients.

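### Part I promises a decision on ZTE MRI as an alternative to CT under a non-inferiority hypothesis, but 30 patients in an exploratory, unsized study can support only an estimate of agreement

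*Protocol article*

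**What the plan says.** The Abstract (Background) sets the hypothesis: "We hypothesize that MRI with a ZTE sequence is non-inferior to CT in terms of fracture morphology specification". The Introduction (Background and rationale) repeats it, with ZTE expected to be "not inferior compared to CT with regard to the detection of fracture lines and specification of fracture morphology". The Abstract (Discussion) says of the ZTE-CT comparison that "it can be decided whether or not the ZTE sequences can be considered as an alternative to CT imaging in proximal humeral fractures", and the main Discussion says the result will be the basis for that judgement.

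Other sections frame the study differently. Background and rationale calls it exploratory, meant to supply data for designing a later investigation. Sample size justification calls it explorative and says that "sample size calculation was omitted". It cites a published minimum of 20 and then, because it is unknown whether DCE MRI fits the biopsy histology, says that "we are considering investigating a total of 30 patients". ZTE against CT plays no part in that number.

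Aim of the study evaluates ZTE "for the assessment of fracture geometry and concomitant injuries compared to CT as the standard of care". The only gold standard named is the biopsy, for humeral head viability (Intraoperative). The main Discussion plans sensitivity and specificity of ZTE without naming the reference. The statistical section describes a normality check and descriptive summaries.

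**The concern.** A non-inferiority claim needs a margin, a level and a sample able to exclude that margin. A decision on replacing CT needs a rule as well. The article makes the claim and promises the decision, but it also states that the sample was not sized, and it ties the number of patients to the other part of the study.

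The comparator adds a second difficulty. With CT as the only standard for morphology, the data can show how often ZTE agrees with CT. They cannot show which modality is right when the two differ.

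At stake is whether CT may be dropped from surgical planning. High concordance in 30 patients could be read as proof of non-inferiority when the interval around it is still wide.

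**Working it through.** **Inputs from the article.** There are 30 patients, each with preoperative CT and ZTE (Design and setting; Table 1). The article gives no margin, level, power or unit of analysis, so it has no calculation to reproduce.

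**Assumed inputs.** One binary result per patient (ZTE agrees with CT or not); CT as reference; exact two-sided 95% limits, so 2.5% on the lower side; margins m of 10, 15 and 20 points. With CT as reference, non-inferiority requires the lower limit of agreement to exceed 1 − m.

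**Step 1: exact (Clopper-Pearson) lower limits at n = 30.** For x = n the limit is 0.025^(1/n), here 0.025^(1/30) = 0.884. For x < n it is the 2.5% quantile of Beta(x, n − x + 1).

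| Agreement | Lower limit |
|---|---|
| 30/30 | 88.4% |
| 29/30 | 82.8% |
| 28/30 | 77.9% |
| 27/30 | 73.5% |

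**Step 2: result needed for each margin.**
- 10 points (limit above 90%): not attainable, since 88.4% is the best possible limit.
- 15 points (above 85%): 30/30 only.
- 20 points (above 80%): at least 29/30.

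**Step 3: chance of that result.**
- 15 points: 0.95^30 = 21.5% if true agreement is 95%; 0.98^30 = 54.5% if it is 98%.
- 20 points: 0.95^30 + 30 × 0.05 × 0.95^29 = 55.4% at 95%; the same sum with 0.98 and 0.02 gives 87.9% at 98%.

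**Step 4: size needed for a 10-point margin.** Under the exact binomial rule at one-sided 2.5% with 80% power, the smallest n is 70 if true agreement is 98% and 231 if it is 95%.

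**Step 5: sensitivity to the assumptions.**
- At one-sided 5%, 30/30 gives 0.05^(1/30) = 90.5%, so a 10-point margin passes, but only with no disagreement. The limits are 85.1% for 29/30 and 80.5% for 28/30, so 15 points then needs 29/30 and 20 points needs 28/30.
- If an independent reference existed and both modalities were equally accurate, approximate power is Φ(m/√(d/30) − 1.96), where d is the proportion of discordant pairs. For m = 0.10 it is 69%, 41% and 23% at d = 5%, 10% and 20%. For m = 0.15 it is 96%, 74% and 45%. For m = 0.20 it is above 99%, 93% and 69%. The normal approximation is rough at d = 5%, where only 0.05 × 30 = 1.5 discordant pairs are expected.

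**The case against.** The strongest reply is that the article is open about its purpose. Directly after the hypotheses it says an exploratory study must come first. The Abstract's Discussion ends with the planning of a randomized trial, and the main Discussion says the data will feed a sample size calculation. The hypothesis can then be read as the premise of a research programme and not as a test in these 30 patients. Omitting a sample size calculation is disclosed and acceptable in such work, and a margin could sit in a full protocol or analysis plan that is not shown.

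Much of this stands. The missing margin and the missing calculation are not faults in themselves. What remains is the sentence promising a decision on ZTE as an alternative to CT, which goes beyond planning a later study. An unseen analysis plan could supply a margin, but not a sample sized for this decision.

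A reader might infer more than the documents support:
- That CT is correct by definition and assigns the AO subtype. The article calls CT the standard of care, lists eligible subtypes without saying which modality assigns them, and says X-ray and CT confirm that there is a fracture. CT as truth is a reasonable inference, because no other morphology reference is named, but it is not stated.
- That MRI-only soft-tissue findings will be scored as MRI errors. No scoring rule is given.
- That non-inferiority will be claimed from a non-significant difference. No ZTE-CT significance test is described.
- That no decision is possible at n = 30. Wider margins, or a one-sided 5% level, can be met with near-perfect agreement. The hypothesis also mentions fracture lines, so the unit of analysis may not be the patient.

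**Conclusion.** The point holds as a conflict within the article: a non-inferiority hypothesis and a promised decision on CT stand beside an exploratory study whose 30 patients were chosen for a different question. Under the stated assumptions, the sample supports the decision only with a wide margin and at most one disagreement in 30 (20 points), or none (15 points). At 10 points it fails whatever the data show, unless a one-sided 5% level is accepted and all 30 agree.

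These figures rest on assumed margins, one binary result per patient, CT as reference and all 30 patients evaluable. The conflict in the text does not depend on them. The planned ZTE-CT data collection is not at fault. What must change is what the study says it may conclude.

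**What to change.** - In the Abstract and in Background and rationale, restate the ZTE hypothesis as an estimation objective: percent agreement and kappa between ZTE and CT for AO group and for fracture features, with exact or otherwise suitable 95% confidence intervals.
- In the Abstract's Discussion, and in the matching sentence of the main Discussion, replace the decision claim with a statement that the agreement estimate and its interval will inform the margin and size of a later non-inferiority study.
- Report discordances in both directions, including for concomitant injuries, without counting findings seen only on MRI as MRI errors.

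This needs no further patients or scans and fits the article's own aim of preparing a later study. The cost is the rewording, the tabulation of discordances and a less favourable claim for ZTE. It does not resolve which modality is right where they disagree; that is left to a later study with a stated reference.

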**Methods:**

This study is designed to investigate the value of modern MRI diagnostics in proximal humeral fractures. 30 patients with an acute unilateral proximal humeral fracture and an indication for ORIF with a locking plate will receive routine diagnostics (conventional X-rays and CT), supplemented by ZTE and DCE 3 Tesla MRI protocols and clinical scores. Two follow-up examinations will be performed at 3 and 6 months after surgery.

**Discussion:**

As the optimal treatment method and timing of proximal humeral fractures are still controversial, the results of this study might help surgeons decide on the optimal treatment. The first aim is to evaluate the ZTE MRI sequence for its ability to assess fracture morphology compared to CT imaging. In this way, it can be decided whether or not the ZTE sequences can be considered as an alternative to CT imaging in proximal humeral fractures. The second aim of the study is to investigate the feasibility of DCE MRI for quantifying perfusion of the humeral head over a six-month period after proximal humeral fracture and ORIF with a locking plate. If the initial DCE MRI shows restricted perfusion of the humeral head, the risk of avascular necrosis may be increased, so it may be beneficial for the patient to proceed directly to reverse shoulder arthroplasty (RSA) instead of osteosynthesis with the risk of later revision. The data obtained from this study are required for the planning of a randomized trial.

**Trial registration:**

DRKS-ID: DRKS00031380, MRI for acute proximal humeral fractures / - Assessment of fracture geometry with an MRI application for imaging cortical bone surfaces (Part I) / - Quantification of humeral head perfusion with Dynamic Contrast-Enhanced MRI (Part II). Acronym: Rostock MRI Study. Date of Registration 2023-06-14. Recruitment is scheduled from 1st July 2023 to 31st December 2024. The final follow-up is scheduled for June 2025. https://drks.de/search/de/trial/DRKS00031380/details;jsessionid=D961FF527EB81204EB9F211810A89B73.

## Introduction

### Background and rationale

With a prevalence of 4–10%, proximal humeral fractures are among the most common fractures and are the third most frequent fractures in the elderly population [1, 2]. Thus far, conventional X-ray imaging and/or computed tomography (CT) are routinely used for the initial detection and characterization of these fractures and subsequent planning of the surgical approach, i.e. open reduction and internal fixation (ORIF) in displaced multifragmentary fracture patterns using a locking plate. However, the functional outcome is mediocre and complication rates are high, especially in elderly patients [3, 4]. Alternative approaches such as conservative therapy, intramedullary nailing, or (reverse) shoulder arthroplasty (RSA) are available, and the decision to apply either one of these techniques remains elusive [5, 6]. Despite increasing evidence that older patients suffering from complex fractures benefit from initial RSA [7], thus far no definite criteria for decision-making are available and the choice of surgical strategy is still controversial [8–10]. Furthermore, concomitant vascular disruption may lead to delayed avascular necrosis of the humeral head with subsequent failure of the fixation procedure and the need for revision surgery [11]. Thus, predicting the risk of humeral head ischemia at the time of fracture would help to reduce the number of patients at risk for revision surgery. Although Hertel et al. proposed a checklist for the evaluation of preoperative radiographs two decades ago, the predictive value of these criteria, e.g. a short dorsomedial metaphyseal extension (< 8 mm), a disruption of the medial hinge, and involvement of the anatomical neck is still controversial [12–14]. While combining all of the proposed criteria allows prediction of ischemia of the humeral head with an accuracy of up to 97%, information on the actual humeral head perfusion is not available via X-ray imaging [15]. However, if vascular necrosis actually occurs, magnetic resonance imaging (MRI) is considered the gold standard for detection [16].

While MRI is routinely chosen for the visualization of soft tissue rather than bony structures, recent developments broaden the field of application for this technique. Firstly, the possibility to apply MRI pulse sequences with ultrashort echo-time (UTE) or even zero echo-time (ZTE) enables imaging of tissues with very short T2/T2* relaxation times and low proton density like the cortical bone [17]. After post-processing, these sequences yield “CT-like” images of bones and have shown their potential value in assessing bone structures when compared to CT imaging in various locations in both, the upper and lower extremity [18–20].

Secondly, dynamic contrast-enhanced MRI (DCE MRI) enables the visualization and quantification of vessel permeability, blood flow, and clearance rates even within bone [21–26].

We hypothesize that *(i)* an MRI including a ZTE sequence is not inferior compared to CT with regard to the detection of fracture lines and specification of fracture morphology and that *(ii)* DCE MRI is suitable for quantifying humeral head perfusion after a proximal humeral fracture.

Because either one of these hypotheses is worth to be investigated within clinical studies, there is the scientific need to conduct an exploratory study first. This will not only provide the data necessary to sharpen the design of a subsequent clinical investigation but will also help to integrate the study investigations into the clinical routine.

## Methods / Design

### Aim of the study

This study aims *(i)* to evaluate a ZTE bone sequence (oZTEo, Signa Premier, General Electric Healthcare, Waukesha, Wisconsin, USA) for the assessment of fracture geometry and concomitant injuries compared to CT as the standard of care, *(ii)* to gain insights into the benefit of a pre-operative DCE MRI for prediction of humeral head perfusion, and *(iii)* to evaluate the humeral head perfusion at 3 and 6 months postoperatively. To this end, the correlation between perfusion data based on DCE MRI, the clinical (scores), and radiological findings (conventional radiographs, CT) as well as the intraoperative findings (biopsy) will be investigated. In parallel, we will compare the preoperative CT and ZTE MRI-based findings with regard to the value for fracture classification. This comparison is indispensable to assess the power of ZTE MRI as a substitute for CT imaging and thus to reduce radiation exposure. Regarding DCE MRI, patients with proximal humeral fractures may benefit from improved preoperative diagnostics and information on the perfusion of the humeral head. This could allow for an individualized decision on optimal treatment and as such may help to reduce the risk for revision surgery.

### Design and setting of the study

This is a prospective, monocentric, non-randomized study investigating the value of modern MRI diagnostics in proximal humeral fractures. The study is conducted at the Department of Traumatology, Hand and Reconstructive Surgery and the Institute of Diagnostic and Interventional Radiology, Pediatric Radiology, and Neuroradiology at Rostock University Medical Center.

Thirty patients with an acute unilateral proximal humeral fracture and a given indication for ORIF with a locking plate will receive routine diagnostics (conventional radiographs and CT), supplemented by ZTE and DCE MRI protocols, and clinical scores. Eligible patients will be informed by trained physicians and have to provide written informed consent to participate prior to any of the study examinations. Two follow-up examinations will be performed at 3 and 6 months after surgery.

### Eligibility criteria

Adults (≥ 18 years of age) presenting with an acute traumatic unilateral proximal humeral fracture of the AO subtypes 11A2.1, 11A2.2, 11A2.3, 11A3, 11B1.1, 11B1.2, 11C1.1, 11C1.3, 11C3.1, 11C3.2 and 11C3.3 and being scheduled for ORIF with a locking plate are eligible. Additional *inclusion criteria* are *(i)* the period between the fracture and the examination must be less than 21 days [27], *(ii)* the willingness to undergo serial MRI examinations, and *(iii)* the ability to give written informed consent. *Exclusion criteria* are any contraindication for MRI and/or the application of contrast-enhancing agents (e.g. claustrophobia, MRI unsafe pacemakers or other implants not compatible for MRI, metallic foreign bodies, allergies, glomerular filtration rate < 30 mL/min/1.73 m^2^ or dialysis), pregnancy or breastfeeding, pathological fractures, stress fractures, previous operations of the affected shoulder, especially with implants in situ, contraindications for ORIF, such as primary glenohumeral osteoarthritis or cuff tear arthropathy. The investigations are taken at baseline, 3 and 6 months postoperatively (Table 1).

**Table 1 Tab1:** Time schedule of the study examinations

	Screening	Intraoperative	Day after surgery	3 month Follow up	6 month Follow up
Inclusion/exclusion criteria	x				
Informed consent	x				
Demographic and medical history	x				
Baseline laboratory test*	x		x	x	x
ZTE and DCE-MRI	x			x	x
X-Ray	x		x	x	x
CT	x				
NRS	x			x	x
SF36	x			x	x
EQ-5D	x			x	x
DASH	x			x	x
SSV	x			x	x
Constant Score				x	x
CCI				x	x
pathology sampling		x			

* Routinely performed serum analysis (thyroid hormones, renal function, blood cell count) plus the determination of Fetuin-A, FGF23, vitamin D and parathormone

### Sample size justification

Due to the fact that this is an explorative study on the feasibility of the imaging techniques mentioned above, sample size calculation was omitted [28]. However, a minimum sample size of 20 participants is recommended, as published elsewhere [29]. As we do not know if the results obtained via DCE MRI fit those obtained via histological examination of the biopsy we are considering investigating a total of 30 patients.

### Subjects

All subjects with a proven unilateral humeral fracture and consent to participate will receive a ZTE MRI and a DCE MRI using a clinical 3.0 Tesla MR-scanner (Signa Premier, General Electric Healthcare, Waukesha, Wisconsin, USA) in a supine position with a 30-channel Adaptive Image Receive (AIR) anterior array surface coil [23]. Patients will be examined prior to, 3 and 6 months following surgery.

### Imaging protocol

The imaging protocol consists of unilateral fat-saturated proton-density (PD) fast spin-echo (FSE) weighted sequences with the PROPELLER technique in the coronal and axial plane, unilateral T1-weighted FSE sequence in the coronal plane, unilateral 3D T1-weighted ZTE bone sequence (oZTEo) in the coronal plane, and a bilateral 3D T2-weighted short tau inversion recovery sequence (STIR) in the coronal plane. After intravenous admission of 0.1 ml Gadobutrol (Gadovist, Bayer Vital, Germany) per kilogram body weight a bilateral T1-weighted FSE DCE sequence with 7 acquisitions and a duration of 5 min as well as a unilateral fat-saturated T1-weighted FSE sequence in the coronal plane will be recorded. Per subject, the time for examination will be around 30 min. Subsequent imaging at 3 and 6 months after surgery will be the same as above plus additional unilateral T1-weighted FSE Flex-sequence and T2-weighted Multi-Acquisition with Variable Resonance Image Combination SeLective (MAVRIC SL) in the coronal plane before contrast admission. Thus, the duration of the examination is estimated at 40 min. DCE sequences will be recorded for both shoulders simultaneously to compare head perfusion of the fractured and the contralateral side. Due to the limited maximum size of the field-of-view (FoV), this will be impossible in patients with a shoulder girdle width of more than 50 cm. In these subjects, only the fractured shoulder will be imaged. The same applies to patients with prior or concomitant shoulder injuries or surgeries on the contralateral side, as a reliable comparison of blood flow is not feasible in these cases either.

